### Outcomes

The primary outcomes of this study will be:

(i) Peak VO_2_;

(ii) Anaerobic threshold;

(iii) Endurance time measured from the constant workload cycle ergometry test;

(iv) HRQoL measured using the CAMPHOR and SF 36 Version 2;

(v) The number of reported acute adverse events (i) reported during exercise training and (ii) resulting in the withdrawal of a subject from the study.

The secondary outcomes of this study will be:

(i) Ventilatory variables at isotime during the constant workload cycle ergometry test (ventilatory equivalent for carbon dioxide [VE/VCO_2_] and end tidal carbon dioxide [PetCO_2_] to describe gas exchange);

(ii) Change in WHO functional class;

(iii) 6MWD (measured from the best of two 6MWTs at each assessment);

(iv) Worsening clinical status (see withdrawal criteria).

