**Design/Methods:**

This randomised controlled trial will determine whether a 12 week, outpatient-based, supervised, whole body exercise training program, followed by a home-based exercise program, is safe and improves exercise capacity and quality of life in individuals with pulmonary arterial hypertension. This study aims to recruit 34 subjects who will be randomly allocated to the exercise group (supervised exercise training 3 times a week for 12 weeks, followed by 3 sessions per week of home exercise for 12 weeks) or the control group (usual medical care). Subjects will be assessed at baseline, 12 weeks and 24 weeks.

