(ii) Exercise training is safe and improvements in exercise capacity will be achieved without evidence of clinical worsening

(iii) An additional 12 week home exercise program will maintain or further improve the benefits gained during the 12 week, supervised, outpatient program.

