### Withdrawal Criteria

Subjects will be withdrawn from the study if they demonstrate deterioration in their clinical status (time to clinical worsening), defined by the presence of two or more of the following [38,39]: (i) escalation of medical therapy (increased dose of medication or commencement of intravenous epoprostenol); (ii) deterioration (≥ 1) in WHO functional class; (iii) development of right heart failure (as indicated by increased jugular venous pressure, new/worsening hepatomegaly, ascites or peripheral oedema); (iv) resting echocardiogram changes (deterioration in right ventricular size and function, right atrial size, pulmonary arterial systolic pressure (PASP) and, where PASP cannot be determined, pulmonary acceleration time); (v) oedema that does not respond to oral diuretics; (vi) hospitalisation for PAH; (vii) listing for transplantation; (viii) ≥ 20% deterioration in 6MWD (ix) progressive worsening of dyspnoea at rest or on exertion over the past 3-5 days [40]; (x) deterioration in ventilatory efficiency (V_E_/VCO_2_) reflecting worsening gas exchange.

Subjects may also be withdrawn from the study at their request or if they experience a serious adverse event during or up to 24 hours following an exercise training session and it is deemed unsafe to continue participation by the treating medical officer from the Royal Perth Hospital Pulmonary Hypertension Service. Adverse events comprise: (i) an incident requiring a medical emergency team call (according to Royal Perth Hospital criteria); (ii) exercise-related incident requiring presentation to the Emergency Department or General Practitioner; (iii) hospital admission due to PAH or worsening right heart failure; (iv) an incident resulting in the patient ceasing exercise during class (chest pain, syncope, worsening dyspnoea despite rests, hypotension/hypertension, bradycardia/tachycardia (as measured by a polar monitor and confirmed by palpation), nausea (associated with sweating, pallor and/or tremor), vagueness, vasovagal, arrhythmia); (v) death.

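### The first limb of the primary adverse-event outcome has no control comparator, and a death or isolated PAH admission outside training is not clearly counted in any outcome

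*Protocol article*

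**What the plan says.** The second hypothesis, at the end of Background, is "Exercise training is safe and improvements in exercise capacity will be achieved without evidence of clinical worsening". Two outcomes address it most directly.

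- **Primary outcome (v), in Outcomes:** "The number of reported acute adverse events (i) reported during exercise training and (ii) resulting in the withdrawal of a subject from the study".
- **Secondary outcome (iv), worsening clinical status:** this refers to Withdrawal Criteria, where deterioration is "defined by the presence of two or more of the following", followed by ten items. Two of the items are "vi) hospitalisation for PAH; (vii) listing for transplantation". Death is not among the ten.

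Withdrawal Criteria also allows withdrawal at the subject's request, or "if they experience a serious adverse event during or up to 24 hours following an exercise training session" where the treating medical officer judges it unsafe to continue. It then lists five kinds of adverse event. Two are bound to exercise: an exercise-related incident leading to an emergency department or general practitioner visit, and an incident that stops exercise in class. Three carry no exercise condition: an emergency team call, "iii) hospital admission due to PAH or worsening right heart failure", and death.

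Subjects are allocated to exercise "or the control group (usual medical care"). Statistical methods compares the primary and secondary outcomes of the two groups by two-way analysis of variance, with transformation or non-parametric tests where normality fails.

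**The concern.** Background explains that exercise has been discouraged in PAH because of feared sudden cardiac death and right heart deterioration. PAH also produces admissions and deaths without exercise. Only the randomised control group can show how many events would have happened anyway, and it can do so only if the same events are counted in the same way over the same period in both groups.

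The first limb of outcome (v) does not do this. A group comparison on that limb sets in-session events against a figure that cannot be anything but zero. The second limb depends on withdrawal, and one of the withdrawal routes is itself tied to sessions. The outcome that does apply equally to both groups leaves out death and does not register a single PAH admission. The most serious events could therefore be missing from the comparison, in one group or both, in a trial intended to inform practice guidelines.

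**Working it through.** The article states no figure for any safety outcome, and its sample size calculation concerns endurance time only. There is no plan figure to reproduce here, so the check is mainly a reading of Outcomes, Withdrawal Criteria and Statistical methods side by side.

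**Step 1: where each event would be counted.** The two limbs of outcome (v) are read as separate counts, as their numbering suggests.

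| Event | Limb (i): during training | Limb (ii): leads to withdrawal | Worsening status (two items needed) |
|---|---|---|---|
| Incident in class, exercise group | Counted | If the subject is withdrawn | Only if two items are met |
| PAH admission alone, control | Impossible | Session-tied route closed; worsening route needs a second item; own request remains | 1 of 2 |
| PAH admission alone, exercise group, more than 24 hours after a session | Not counted | As for a control | 1 of 2 |
| Death, control | Impossible | Only if death is read as withdrawal, which the text does not say | 0 of 2 from the death itself |
| Death, exercise group, more than 24 hours after a session | Not counted | As for a control | 0 of 2 from the death itself |
| Transplant listing alone, either group | Not a listed adverse event | Worsening route needs a second item | 1 of 2 |

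**Step 2: do the other two-arm measures fill the gap?** WHO class and 6MWD are measured in both groups. They do not record a death. In the intention-to-treat analysis, missing 12- and 24-week values are replaced by the last observation, so a subject who died would, under that stated rule, keep the last value from before death.

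**Step 3: does the analysis method rescue limb (i)?** No. Moving from analysis of variance to a rank test changes the test, but the control value remains zero by construction.

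**Step 4: how much could a clean record show?** With 0 events in n subjects, the exact two-sided 95% upper limit p solves (1 − p)^n = 0.025, so p = 1 − 0.025^(1/n).

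- n = 17 (recruited per group, Sample size calculation): 1 − 0.025^(1/17) = 0.195, or 19.5%.
- n = 14 (the group size used for power): 1 − 0.025^(1/14) = 0.232, or 23.2%.

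**Step 5: what could a two-arm count detect?** For k events against 0 with 17 per group, Fisher's two-sided p is 2 × C(17,k)/C(34,k).

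- k = 4: 2 × 2380/46376 = 0.103.
- k = 5: 2 × 6188/278256 = 0.044.

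At least 5 events against 0 are needed for p < 0.05. Steps 4 and 5 follow from the group size, not from the outcome definitions. They bear on how the safety conclusion should be worded.

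**The case against.** Three stronger readings are tempting, and the article does not support them.

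- **That the whole control count is fixed at zero.** A reader might infer this from the session wording. It holds for limb (i) and for the serious-adverse-event withdrawal route only. Limb (ii) is not confined to the exercise group, three of the five listed adverse events have no exercise condition, and any subject can be withdrawn for clinical worsening. A control admitted for PAH who meets one further worsening item can enter limb (ii).
- **That the trial cannot answer its safety question.** Worsening status, WHO class and 6MWD are compared between randomised groups and address the second hypothesis in part. Limb (i) is also a sensible description of tolerance in class.
- **That echocardiographic or ventilatory drift would often count as worsening by chance.** No size is given for those items, but a condensed article may leave thresholds to the full protocol. Any rate would have to be assumed.

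It can also be said that an isolated PAH admission is a narrow gap, because an admitted patient may well meet a second item such as escalated therapy or a worse functional class. That is fair, and the article gives no frequency either way. It does not help with death, which is not an item at all. Finally, symmetric counting would add little power with 17 per group. That also stands: the gain is an unbiased comparison, not a sensitive one.

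**Conclusion.** The concern holds in a limited form. Limb (i) of a primary outcome has no valid control comparator, so the group comparison prescribed in Statistical methods does not fit it. Deaths, and isolated PAH admissions outside the session window, are listed as adverse events but are not clearly counted in any outcome. An isolated transplant listing likewise falls short of worsening status.

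The number of events affected cannot be stated, because the article gives no background rates. The conclusion rests on reading the two limbs as separate counts and on not treating death as withdrawal, which the text does not say. Whatever the definitions, a record of no events in 17 would leave risks of up to 19.5% open. That does not support an unqualified statement that training is safe.

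**What to change.** 1. Redefine the comparative part of outcome (v). In both groups, count emergency team calls, admissions for PAH or right heart failure, deaths, and any emergency department or general practitioner presentation. Count from randomisation to week 24, whether or not a session was near and whether or not the subject has been withdrawn.
2. Report the number of subjects with an event in each group and the group difference with exact 95% limits, in place of analysis of variance.
3. Keep in-class events as a description of the exercise group only, with no between-group test.
4. Word the safety conclusion as event rates with their upper limits.
5. Reconcile Outcomes with Withdrawal Criteria by stating how death, and an isolated PAH admission or transplant listing, count in secondary outcome (iv). This concerns the outcome only; the withdrawal rule stays with the clinicians.

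The cost is revised outcome wording and one event question put to both groups at the existing 12- and 24-week assessments, with the same question followed up for subjects who have been withdrawn. It should be settled early, because control-group events that were not collected may not be recoverable later.

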### Sample size calculation

Improvements in endurance time following exercise training have recently been reported in the PAH population [10]. These authors [10] reported a mean increase in endurance time, as measured from a constant workload cycle ergometer test, of 270 seconds. The constant workload tests were set at 75% of the peak workload achieved during the incremental CPET, which is consistent with our study's protocol. The mean endurance time (standard deviation) at baseline and post-training were 390 (40) and 660 (60) seconds respectively.

Conservative sample size calculations have been performed using a two-sided Mann-Whitney U test, assuming that the actual distribution is a double exponential. Group sizes of 14 will achieve 91% power to detect a difference of 200 seconds between the null hypothesis that both group means are 600 seconds and the alternative hypothesis that the mean of group 2 is 400 seconds with estimated group standard deviations of 180 and 120 and with a significance level (alpha) of 0.01.

A total of 34 subjects (17 in the exercise group and 17 controls) will be recruited to allow for 20% attrition of subjects from the per protocol analysis.

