### Statistical methods

Data will be analysed using SPSS software (Version 17.0; SPSS Inc; Chi). Data that are not normally distributed will be transformed and if transformation fails to satisfy normality, non-parametric tests will be used. The primary and secondary outcomes in the exercise and control groups will be compared using two-way analysis of variance to account for group and time interactions. Statistical relationships between outcome variables will be analysed using Pearson's or Spearman's correlations as appropriate. Data will be analysed using (i) per protocol analysis and (ii) intention-to-treat analysis. Per protocol analysis will be restricted to the data from subjects who complete all assessments and for the exercise group who attend at least 75% of their exercise classes. The required number of sessions must be achieved within a period of 15 weeks for both the supervised and home exercise training programs, allowing for intercurrent illness and other factors that may impact on an individual's ability to attend sessions. The last-observation-carried-forward method will be used to impute missing data at 12 and 24 weeks for the intention-to-treat analysis [41]. The Berger-Exner [42] test will be carried out to determine whether selection bias has been introduced into the study.

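### The 91% power is a large-sample approximation: the plan's own Mann-Whitney inputs give about 80% at 14 per group, the assumed distribution is favourable, and that test is only the fallback analysis

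*Protocol article*

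**What the plan says.** All the sizing is in the Sample size calculation section of the protocol article. It reports that "Conservative sample size calculations have been performed using a two-sided Mann-Whitney U test, assuming that the actual distribution is a double exponential". The result is that "Group sizes of 14 will achieve 91% power to detect a difference of 200 seconds". The hypotheses compared are "the null hypothesis that both group means are 600 seconds and the alternative hypothesis that the mean of group 2 is 400 seconds". The other inputs are SDs of 180 s and 120 s and an alpha of 0.01. On recruitment it says: "A total of 34 subjects (17 in the exercise group and 17 controls) will be recruited to allow for 20% attrition".

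The background for these inputs is a cited training study that "reported a mean increase in endurance time, as measured from a constant workload cycle ergometer test, of 270 seconds", with SDs of 40 s at baseline and 60 s after training.

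The Statistical methods section says that the primary and secondary outcomes "will be compared using two-way analysis of variance to account for group and time interactions". Non-normal data are transformed first, and non-parametric tests are used only if transformation fails.

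**The concern.** Three things do not fit together.

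- **The figure.** A rank test with 14 per group at alpha 0.01 would need an unusually favourable distribution to reach 91% with a standardised difference of about 1.3.
- **The label.** Of the usual distributional choices for a Mann-Whitney power calculation, the double exponential is the one that helps the test most, yet the sentence opens by calling the calculation conservative.
- **The test.** The test that was sized is the last resort in the analysis section, and the test planned first was not sized.

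Endurance time is the only one of the five listed primary outcomes that the section sizes. If the trial finds no difference on it, readers will weigh that result against a stated 9% chance of missing a 200 s effect. If that chance is really about twice as large under the plan's own model, the null result would be over-read. The article expects the trial to contribute to clinical practice guidelines.

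**Working it through.** **Inputs** (all from Sample size calculation): means 600 and 400 s, difference 200 s; SDs 180 and 120 s; n = 14 per group; two-sided alpha 0.01; double-exponential data; Mann-Whitney test.

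**Step 1. Standardised difference.** Root-mean-square SD = sqrt((180² + 120²)/2) = sqrt(23,400) = 153.0 s, so d = 200/153.0 = 1.307.

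**Step 2. Reproduce the stated 91%.** The usual approximation takes the two-sample t-test power and multiplies n by the asymptotic relative efficiency of Mann-Whitney against the t-test. For the double exponential this is 1.5, so 14 becomes 14 × 1.5 = 21.

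- Standard error at n = 21: sqrt((180² + 120²)/21) = sqrt(46,800/21) = 47.2 s. Noncentrality = 200/47.2 = 4.24.
- Welch degrees of freedom from the real n = 14: 13 × 46,800²/(180⁴ + 120⁴) = 22.6. Power = **91.0%**.
- Degrees of freedom also from n = 21: 92.7% (Welch) or 93.1% (pooled).

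The stated figure is therefore the output of this approximation.

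**Step 3. Simulate the stated model.** Double-exponential samples were drawn with means 600 and 400 and scale parameters SD/√2 (127.3 and 84.9), with 40,000 runs. The Monte Carlo standard error is about sqrt(0.8 × 0.2/40,000) = 0.2 percentage points. Normal samples with the same means and SDs were run for comparison.

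| Test, two-sided alpha 0.01 | 14 per group | 17 per group |
|---|---|---|
| Mann-Whitney, double exponential, asymptotic p | 79.4% | 89.5% |
| Mann-Whitney, double exponential, exact p | 80.9% | 90.2% |
| Mann-Whitney, normal, asymptotic p | 68.5% | 80.9% |
| Mann-Whitney, normal, exact p | 70.5% | 82.0% |
| Pooled t-test, double exponential | 75.3% | 84.2% |
| Pooled t-test, normal | 74.5% | 84.8% |

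Under the plan's own model, the chance of missing a true 200 s difference with 14 per group is 19-21%, not 9%.

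**Step 4. Compare distributions by the efficiency method of Step 2** (Welch degrees of freedom from the scaled n). Double exponential (n acts as 21): 92.7%. Logistic (15.35): 78.9%. Uniform (14): 73.5%. Normal (13.37): 70.6%. The double exponential is the most favourable of the four.

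**Step 5. Parametric comparison at one time point.** Standard error at n = 14: sqrt(46,800/14) = 57.8 s. Noncentrality = 200/57.8 = 3.46 on 26 degrees of freedom. Power = **74.6%** (pooled t, equal to the ANOVA F test at one time point; Welch 73.5%). With 17 per group it is 85.0%. About 20 completers per group would be needed for 91%.

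**Step 6. Group-by-time comparison.** This needs the within-subject correlation ρ, which the article does not give. Assume equal SDs over time, so that each SD of change is SD × sqrt(2(1 − ρ)). With 14 per group and alpha 0.01:

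| ρ (assumed) | 0 | 0.3 | 0.5 | 0.6 | 0.7 | 0.8 |
|---|---|---|---|---|---|---|
| Change contrast | 39% | 56% | 75% | 85% | 95% | 99% |
| Baseline-adjusted ANCOVA, SD × sqrt(1 − ρ²) | 75% | 79% | 88% | 93% | 97% | 99.7% |

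**The case against.** Several points on the other side are sound.

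- **The word conservative has a fair reading.** The plan sizes on 200 s where the cited study saw 270 s, and on SDs of 180 and 120 s where that study had 40 and 60 s. With the cited 270 s and the inflated SDs, a plain t-test with 14 per group at alpha 0.01 has 96% power. This stands for the effect and the SDs. It does not carry over to the distribution, to which the sentence ties the word and which raises the power.
- **A reader might infer that the planned ANOVA has 75% power.** The article does not support that. The 74.6% belongs to a comparison at one time point. The planned group-by-time analysis matches it only at a correlation near 0.5, and could fall well below it or above 91%.
- **A reader might infer an arithmetic slip.** There is none: 91% follows from the approximation. The fault is that the approximation does not hold at this n and alpha.
- **Rank tests do have a place in the plan.** They are the stated fallback, and the 20-minute cap on loaded cycling makes non-normal data possible. The two SDs are also the same fraction of their means (180/600 = 120/400 = 0.30). If the data were lognormal, which is an assumption, the transformation route would give about 80% with 14 per group and 89% with 17. None of this brings the stated calculation to 91% at 14.
- **Fourteen per group is the number left after attrition.** With all 17, the stated model gives about 90%. But the article attaches the 91% to 14. Its intention-to-treat analysis reaches 17 by carrying earlier values forward, so the 17-per-group figures hold only if the carried-forward subjects also show the full difference.

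**Conclusion.** The stated power is wrong as written. For the test, distribution, difference, SDs, alpha and group size that the article names, power is about 79-81%, roughly 10 to 12 percentage points below the stated 91%. The chance of a miss is about double the stated 9%. This rests only on the article's own inputs.

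The distributional assumption is favourable, not conservative: changing it to normal lowers the same test to about 69-71%. The sized test and the first-line analysis also differ, so the 91% does not describe the planned analysis.

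A reader might go further and conclude that the trial as a whole is underpowered, or that its miss rate is two to three times the stated one. That does not follow. The planned analysis uses repeated measurements, and its power runs from 39% to 99% over assumed correlations of 0 to 0.8. What can be said is that the article gives no basis for 91%.

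**What to change.** In Sample size calculation:

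1. Restate the power with 14 per group and alpha 0.01 as about 80% for Mann-Whitney under the stated double-exponential model, and about 75% for a parametric comparison at a single time point.
2. Keep the word conservative, if at all, for the effect size and SDs, and do not apply it to the distribution.
3. Base the sample-size statement on the analysis named in Statistical methods, with a stated within-subject correlation and its source, or with a range such as the one above.

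If more power is wanted from the same patients, a baseline-adjusted ANCOVA uses data already collected. It would have about 87-88% at an assumed correlation of 0.5 and 97% at 0.7. It would need naming in Statistical methods as well.

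The cost is a wording change and a less favourable stated figure, with no added patients. Moving to alpha 0.05 or to a single primary outcome would also change the power, but that is a design trade-off for the sponsor and not part of this correction.

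### Recruiting 17 per group does not quite allow for the stated 20% attrition: 13.6 per group would remain in the per protocol analysis against the 14 required, a shortfall of under one patient overall

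*Protocol article*

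**What the plan says.** All the figures stand in the Sample size calculation section of the protocol article.

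- Required size and power: "Group sizes of 14 will achieve 91% power to detect a difference of 200 seconds".
- Test and distribution: "two-sided Mann-Whitney U test, assuming that the actual distribution is a double exponential".
- Means compared: "both group means are 600 seconds and the alternative hypothesis that the mean of group 2 is 400 seconds". The assumed SDs are 180 s and 120 s, and alpha is 0.01.
- Recruitment: "A total of 34 subjects (17 in the exercise group and 17 controls) will be recruited to allow for 20% attrition of subjects". The loss meant is loss to the per protocol set.

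The Statistical methods section limits the per protocol set to subjects with every assessment and, in the exercise group, attendance at no less than three quarters of the classes. It also plans an intention-to-treat analysis, in which missing 12- and 24-week values are imputed by last observation carried forward.

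**The concern.** An attrition allowance is meant to ensure that, after the stated loss, the number behind the power statement is still there. To do that, the required number is divided by the fraction retained. Here the retained fraction is 0.8 and the required number is 14, and 17 recruited per group falls just short. The article therefore makes a claim about its own sample size that its own figures do not bear out.

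What is at stake is modest but visible. The trial report will set the achieved per protocol numbers beside this sentence. A reader who takes it at face value will believe that a loss of one subject in five leaves 14 per group, when a fourth loss in a group of 17 already leaves 13. Subjects can leave the per protocol set by missing an assessment, by low class attendance (exercise group only), by clinical worsening, or by withdrawal at their own request or after a serious adverse event. The losses need not be equal between groups.

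**Working it through.** **Inputs** (protocol article, Sample size calculation): 14 evaluable per group (28 in total); 17 recruited per group (34 in total); attrition 20%; difference 200 s (600 versus 400 s); SDs 180 and 120 s; two-sided alpha 0.01; Mann-Whitney test under a double exponential distribution.

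**1. Reproducing the stated 34.** The article does not show the step from 28 to 34. Two routes give the number:

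- Multiplying by 1 + 0.2: 28 × 1.2 = 33.6, rounded to 34; per group 14 × 1.2 = 16.8, rounded to 17.
- Dividing by 1 − 0.2 and rounding down: 14/0.8 = 17.5, taken as 17 per group, so 34.

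**2. What remains after 20% attrition.**

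- Per group: 17 × 0.8 = 13.6, against 14 (short by 0.4).
- In total: 34 × 0.8 = 27.2, against 28 (short by 0.8).

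**3. What 34 does tolerate.** 17 − 14 = 3 losses per group; 3/17 = 17.6%. A fourth loss (4/17 = 23.5%) leaves 13.

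**4. What 20% would require.** 28/0.8 = 35 in total; with equal whole groups, 18 per group (36), since 18 × 0.8 = 14.4. That is 1 or 2 more than 34.

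**5. Effect on power.** The approximation that comes nearest to the stated 91% uses the asymptotic relative efficiency of the Mann-Whitney test under a double exponential distribution, which is 1.5. The effective size is m = 1.5 × n per group, and power comes from a noncentral t distribution with noncentrality 200 / √((180² + 120²)/m) = 200 / √(46,800/m).

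| n per group | m | Noncentrality | Power, pooled df | Power, unequal-variance df |
|---|---|---|---|---|
| 14 | 21 | 200/47.2 = 4.24 | 93.1% | 92.7% |
| 13.6 | 20.4 | 200/47.9 = 4.18 | 92.2% | 91.8% |
| 13 | 19.5 | 200/49.0 = 4.08 | 90.7% | 90.2% |

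At 14 per group this lies about 2 points above the stated 91%, so it is close but not an exact reproduction, and the differences are more reliable than the levels. The loss is 0.9 points from 14 to 13.6 and 2.4 to 2.5 points from 14 to 13. Taken off the stated figure instead, that would be 91 − 0.9 = 90.1% and 91 − 2.5 = 88.5%.

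**6. How often 14 would be kept.** As an illustration only, assume that each subject leaves the per protocol set independently with probability 0.2. A group of 17 then keeps at least 14 with probability 0.549, and both groups do so with probability 0.549² = 0.30. With 18 per group the figures are 0.716 and 0.51. No planning figure guarantees 14, but 17 per group has no reserve at the stated rate.

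**The case against.** The strongest reply is that this is rounding. Subjects are lost whole: 20% of 17 is 3.4, and losing 3 leaves exactly 14. A planning rate of 20% is itself a guess, and 17.6% is close to it. The shortfall is 0.8 of a patient overall, and the recruited number is within 2 of any correct answer. All of this stands and sets the severity. It does not make the sentence true, because at the rate it names the expected number is below 14.

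Three stronger readings are tempting, and the document supports none of them.

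- *The stated 91% power is lost.* By the approximation above, power at 13.6 per group is 91.8 to 92.2%, not below 91%; at 13 per group it is 90.2 to 90.7%, marginally below. A normal-theory t-test gives 74.6% at 14 and 70.0% at 13, but the article did not size the trial on that test. The gap between 91% and 75% concerns the power method, not attrition. Direct simulation of the Mann-Whitney test with double exponential data gave about 79% at 14 and 74% at 13. On that basis one subject per group costs about 5 points, but whether 91% is right at all is a separate question and lends no weight here.
- *The error is known to be multiplication by 1.2.* The figures fit exactly, but rounding 17.5 down to 17 fits equally well and the derivation is not shown.
- *The whole trial is undersized.* The allowance is tied to the per protocol analysis. The intention-to-treat analysis imputes missing follow-up values and is planned to keep all 17 per group.

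**Conclusion.** The point holds as a small internal inconsistency. The article's 17 per group allows for 17.6% attrition, not 20%; at 20%, 13.6 per group remain against the 14 on which the power is stated. This follows from the article's own numbers and does not depend on any power method.

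The consequence is minor: under one patient overall, about 1 point of power at 13.6 per group and about 2.5 points if both groups fall to 13. Those power figures assume the efficiency-adjusted approximation with a factor of 1.5, equal losses in the two groups, and the article's stated difference, SDs and alpha. Only the per protocol analysis is affected. Low severity: the sentence should be corrected, but the design and the number recruited can stay as they are.

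**What to change.** Change one sentence in the Sample size calculation section, in either of two ways.

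- Keep 34 and state the allowance that it gives: up to 3 of 17 subjects per group (17.6%) may be lost from the per protocol analysis while 14 per group remain.
- Keep the 20% rate and state that 13 to 14 per group are then expected in the per protocol analysis, with the power for those sizes recomputed by the method that gave 91%.

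Showing the step from 28 to the recruited total would remove any doubt about how it was reached. Neither option needs extra patients or alters the design or analysis. The cost is a slightly less favourable stated figure, either for attrition or for power. Recruiting 18 per group would also close the gap, for 2 more patients, but the size of the effect does not call for it.
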